### *Primary and secondary outcome measures*

The primary outcome will be the hemoglobin A1c at six months adjusted for the baseline measurement (the most recent result during the 3 months prior to enrollment). Hemoglobin A1c is associated with mortality and both macrovascular and microvascular complications of diabetes. Changes in hemoglobin A1c of 0.4 % or greater are associated with clinically important reductions in at least microvascular diabetes complications. The hemoglobin A1c will be obtained through chart reviews and by accessing laboratory data with consent. If more than one hemoglobin A1c measurement is available between 3 and 6 months (even though the test is usually done every 3 months or less frequently), only the later one will be used. The primary analysis will include all participants and report A1c as a continuous measure. We will also report the change in hemoglobin A1c by condition ("prediabetes" and diabetes), the number of participants with "pre-diabetes" (A1c 6.0 to 6.4) at baseline who convert to a normal hemoglobin A1c ( $<6.0\%$ ) and those who convert to diabetes ( $A1c \geq 6.5$ ), and the number of participants with diabetes at baseline ( $A1c \geq 6.5$ ) who convert to "pre-diabetes" (A1c 6.0 to 6.4) and to normal hemoglobin A1c ( $<6.0\%$ ).

### *Secondary outcome measures*

Secondary outcomes will include self-reported health, self-reported food-security, self-reported financial security, carotenoid level, and self-reported fruit and vegetable consumption. Carotenoid levels will be measured during a visit at the end of the study (months 5 or 6). Serum levels of  $\alpha$ -carotene,  $\beta$ -carotene, lutein,  $\beta$ -cryptoxanthin, and ascorbic acid correlate with self-reported vegetable and fruit consumption although the absolute value varies based on characteristics of the individual such as age and body mass index. It is thus an appropriate measure to use as a trial outcome. Self-reported health status is associated with mortality and is based on both current health and perceived health risks. The standard question is: "In general, how would you rate your health today?" Potential responses are: very good, good, moderate, bad, very bad and decline to respond. Self-reported food security will be assessed with three standard questions: "In the past 30 days, have you been concerned about having enough food for you or your family?" Potential responses are: yes, no and decline to respond. "Food you and other household members bought didn't last and there wasn't any money to get more?" Potential responses are: yes, no and decline to respond. Self-reported food security (balance): "You and other household members couldn't afford to eat balanced meals?" Potential responses are: yes, no and decline to respond. Self-reported vegetable consumption will be assessed using the standards question "How often to you eat vegetables?" Potential responses include: 0 times per day, once per day, twice per day, three times per day, four times per day, five or more times per day, or decline to answer. The same question will be applied to fruit consumption. Self-reported financial security will be assessed using the standard question "Do you have trouble making ends meet at the end of the month?"(44) Potential responses are: yes, no and decline to respond. We will ask about trade-offs between food and diabetes supplies, that is, whether participants put off purchasing food to buy diabetes supplies or vice versa (never, sometimes, often, regularly). We will track changes in medicines including changes in dose based on information available in the electronic health records. We will also

ask participants in the intervention group how often they accessed the food retailer, about their participation in educational and community building activities, about wasted food and about whether they would have wanted other foods to be provided.

We will perform a cost-effectiveness analysis from a societal perspective that considers direct and indirect costs of the intervention and direct and indirect effects including changes in healthcare utilization. We will assess the economic implications of the potential effects of the intervention including costs associated with primary care, emergency department use, and complications of diabetes based on previous studies of the association between hemoglobin A1c and health outcomes.

We will report demographic characteristics collected at the time of enrollment including age, sex, gender, education level, household income, income source, ethnicity, and medical comorbidities.

We will employ an intention to treat analysis. The primary analysis of the follow-up A1c (follow-up measurement) will be adjusted for baseline hemoglobin A1c and analysed using analysis of covariance (ANCOVA). Binary outcomes will be compared between groups using risk differences with 95% confidence intervals, and chi-squared tests to derive two-sided p-values. Continuous outcomes will be compared between groups using difference in means with 95% confidence intervals, and t-tests to derive two-sided p values. Count outcomes will be analysed using rate ratios from quasi-Poisson models with 95% confidence intervals and two-sided p-values, which will be adjusted for baseline values whenever available. Ordinal outcomes will be analyzed using ordinal regression.

Randomization will be stratified by site. We will report both the unadjusted analysis for the primary outcome and the analysis adjusted for age, sex, whether or not prescribed diabetes oral medicines at baseline, and whether or not prescribed insulin at baseline.

A subset of 20 randomly selected intervention group participants will be prompted to report all foods and beverages consumed the prior day using a validated self-administered 24-hour recall (ASA24 <http://riskfactor.cancer.gov/tools/instruments/asa24/>). In a separate subset of 20 purposefully selected intervention group participants, we will conduct one-on-one interviews over the phone to capture the experience of the intervention for qualitative analysis. If participants agree, the interviews will be audio recorded. The transcripts will then be coded and analyzed by two research coordinators. The results of these studies will be reported together.

We will present results by diagnosis (diabetes versus “prediabetes”), age, sex, gender and income level.

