## **Inclusion/Exclusion Criteria**

Participants will be adult (age >19 years) patients of the two participating primary care who have either “pre-diabetes” (A1c 6.0 to 6.4) or diabetes (A1c  $\geq$  6.5) based on bloodwork done in the last 3 months and who either score 2 or above on the six-item food insecurity instrument or who report trouble “making ends meet”. We will exclude people who live with a current study participant (to avoid contamination), people who are palliative (have a life expectancy < 6 months), people with multiple (>3) life-threatening allergies to common foods, people who require total parenteral nutrition, and people with a blood dyscrasia that interferes with hemoglobin A1c testing (anemia due to iron deficiency, B12 deficiency and folate deficiency). We will also exclude individuals with very poorly controlled diabetes (A1c > 11) as interventions other than food such as medicines may be the most important interventions. We will also exclude individuals with very poorly controlled diabetes (A1c > 11) as interventions other than food such as medicines may be the most important interventions.

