###### 3.2 The secondary objectives of this trial are to test the following hypotheses:

1. A monthly subsidy of \$65 (or \$85) for healthy food every month for six months is superior to usual care in its effect on beta-carotene in adults with type 2 diabetes or “prediabetes” experiencing food insecurity or trouble making ends meet

2. A monthly subsidy of \$65 (or \$85) for healthy food every month for six months is superior to usual care in its effect on ascorbic acid in adults with type 2 diabetes or “prediabetes” experiencing food insecurity or trouble making ends meet
3. A monthly subsidy of \$65 (or \$85) for healthy food every month for six months is superior to usual care in its effect on self-reported health status in adults with type 2 diabetes or “prediabetes” experiencing food insecurity or trouble making ends meet
4. A monthly subsidy of \$65 (or \$85) for healthy food every month for six months is superior to usual care in its effect on self-reported financial security in adults with type 2 diabetes or “prediabetes” experiencing food insecurity or trouble making ends meet
5. A monthly subsidy of \$65 (or \$85) for healthy food every month for six months is superior to usual care in its effect on food security status in adults with type 2 diabetes or “prediabetes” experiencing food insecurity or trouble making ends meet
6. A monthly subsidy of \$65 (or \$85) for healthy food every month for six months is superior to usual care in its effect on self-reported vegetable consumption in adults with type 2 diabetes or “prediabetes” experiencing food insecurity or trouble making ends meet
7. A monthly subsidy of \$65 (or \$85) for healthy food every month for six months is superior to usual care in its effect on self-reported fruit consumption in adults with type 2 diabetes or “prediabetes” experiencing food insecurity or trouble making ends meet

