  - a. (If answered Yes to question 3) How often did this happen? Potential responses are: Almost every month, Some months but not every month, Only 1 or 2 months, Don't know/Refuse to answer
4. In the past 6 months, did you (personally) ever eat less than you felt you should because there wasn't enough money to buy food

5. In the past 6 months, were you (personally) ever hungry but didn't eat because you couldn't afford enough food? Potential responses are: Yes, No, Don't know/Refuse to

Participants can answer affirmatively to 0 to 6 of the questions. We will assess food security status as a binary variable, where less than 2 affirmative responses indicates "food secure" and 2 or more affirmative responses indicates more "food insecure." This is based on Health Canada's approach to interpreting the data from the Household Food Security Survey Module (13). We will also examine food security as a raw score between 0 to 6 (based on the number of affirmatively answered questions) as a sensitivity analysis.

Self-reported financial security is a categorical variable where participants were asked the standard question at follow-up "Do you have trouble making ends meet at the end of the month?" Potential responses were: yes, no and decline to respond.

Self-reported vegetable consumption and self-reported fruit consumption are both categorical variables, measured at both baseline and 6 months. Participants were asked "How often to you eat vegetables?" and "How often do you eat fruits?" Potential responses included: 0 times per day, once per day, twice per day, three times per day, four times per day, five or more times per day, or decline to answer.

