### 8.3 Analysis of secondary outcomes

The continuous outcomes of serum  $\beta$ -carotene and ascorbic acid levels will be compared between groups using difference in means with 95% confidence intervals, and t-tests will be used to derive two-sided  $p$ -values. Alternative non-parametric tests will be used if the data does not meet the assumptions of t-tests and these may include the Wilcoxon Rank Sum test.

The binary outcomes of self-reported financial security and food security status will be compared between groups using risk differences with 95% confidence intervals, and chi-squared tests to derive two-sided  $p$ -values.

The count outcomes of self-reported vegetable and fruit consumption, will be compared between groups using the Wilcoxon rank sum test, where a  $p$ -value of  $<0.05$  will be sufficient to reject the null hypothesis of no difference.

For the ordinal outcomes of self-reported health-status and food-security score ordinal regression will be used using odds ratios with 95% confidence intervals.

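### Financial security at six months (secondary hypothesis 4) is compared by a crude risk difference that uses no baseline information or randomisation stratum: valid, but possibly less precise than the trial's own data allow

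*Combined protocol and SAP*

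**What the plan says.** **Entry.** The protocol's Inclusion/Exclusion Criteria admit people who "either score 2 or above on the six-item food insecurity instrument or who report trouble" making ends meet. The two routes are alternatives, so a person can enter on the food score alone.

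**Outcome.** Under Secondary outcome measures, "Self-reported financial security will be assessed using the standard question" on trouble making ends meet at the end of the month, with answers yes, no or decline. SAP 3.2 makes it the fourth secondary hypothesis, that the voucher is "superior to usual care in its effect on self-reported financial security in adults" of the trial's target population. SAP 6.3 lists it as binary.

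**Baseline.** SAP 5.3 states: "Self-reported financial security is a categorical variable where participants were asked the standard question at follow-up". That section lists baseline survey data for food security and for vegetable and fruit intake. Financial security is not in the list.

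**Analysis.** The protocol's analysis paragraph gives binary outcomes a risk difference with a chi-squared test. SAP 8.3 does the same: the "binary outcomes of self-reported financial security and food security status will be compared between groups using risk differences", again with a chi-squared p-value. Neither names a covariate or stratum. In that protocol paragraph, count outcomes are to be modelled with results "which will be adjusted for baseline values whenever available". The covariates in SAP 8.2 are for A1c only.

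**Stratum.** The protocol's Design section and SAP 2.2 say randomisation is stratified by condition (prediabetes or diabetes). The protocol's analysis paragraph says it is stratified by site.

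**The concern.** The either/or entry rule can mix two kinds of participant. Those who enter reporting trouble making ends meet can improve by six months. Those admitted on the food score alone may start without such trouble and can then only stay the same or worsen. If the starting position varies and persists, it predicts the six-month answer, and a crude comparison leaves that predictable variation in the error term. A randomisation stratum that predicts the outcome is lost in the same way.

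At stake is the width of one confidence interval and the power of one secondary test. The outcome matters to the trial's argument because it bears directly on the rationale, given in both documents, that food support frees money for other needs. The trial was sized for A1c alone, and SAP section 7 reports recruitment complete at 390, so the analysis is the remaining place to gain precision.

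**Working it through.** **1. The plan's own figure.** The only sample size calculation is for A1c (SAP section 7: SD 1.3, difference 0.4, two-sided alpha 0.05 assumed, power 80%).

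n per arm = 2 × (1.96 + 0.842)² × 1.3² / 0.4² = 165.8, so 166 per arm and 332 in all. Then 332 / 0.85 = 390.6, against the stated 390. The figure reproduces to rounding. Neither document gives a power or precision figure for financial security. The 166 per arm is used below as the evaluable number.

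**2. Variance explained by the entry answer.** Let q be the proportion answering yes at entry, and p1 and p0 the six-month yes proportions among entry-yes and entry-no participants. Then

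P = q·p1 + (1 − q)·p0, and r² = q(1 − q)(p1 − p0)² / [P(1 − P)].

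The adjusted variance is about (1 − r²) times the crude variance, equivalent to a sample larger by the factor 1/(1 − r²). The documents supply none of q, p1 or p0, so every rate here is an assumption.

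| Entry yes (q) | 75% v 45% | 75% v 30% | 85% v 30% |
|---|---|---|---|
| 60% | 0.093 | 0.198 | 0.311 |
| 80% | 0.067 | 0.144 | 0.252 |
| 90% | 0.040 | 0.088 | 0.167 |
| 95% | 0.022 | 0.049 | 0.098 |
| 100% | 0 | 0 | 0 |

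For q from 60% to 90%, r² runs from 0.040 to 0.311, equivalent to about 4% to 45% more participants.

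**3. A middle case.** With q = 0.80, p1 = 0.75 and p0 = 0.30: P = 0.66 and r² = 0.16 × 0.2025 / 0.2244 = 0.144. Then 1/(1 − 0.144) = 1.17, or about 56 extra on 332.

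For an assumed 15-point reduction (66% to 51%) with 166 per arm:

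- Crude SE = √[(0.66 × 0.34 + 0.51 × 0.49)/166] = 0.0534; 95% half-width 10.5 points; power Φ(0.15/0.0534 − 1.96) ≈ 80%.
- Adjusted SE = 0.0534 × √(1 − 0.144) = 0.0494; half-width 9.7 points; power ≈ 86%.

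For smaller effects in the same case, power goes from 47% to 53% at 10 points and from 16% to 18% at 5 points.

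**4. Simulation check.** Crude chi-squared was set against a Mantel-Haenszel analysis stratified by entry answer, with 8,000 trials per setting and 166 per arm. Type I error of the crude test was 4.7% to 5.5%, and both estimates were unbiased. Power for a 15-point reduction:

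| Entry yes | Six-month yes, by entry answer | Crude | Stratified |
|---|---|---|---|
| 80% | 80% v 50% | 83% | 85% |
| 80% | 80% v 30% | 81% | 88% |
| 80% | 90% v 20% | 84% | 96% |
| 95% | 80% v 30% | 85% | 87% |

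The 90% v 20% row is a stronger persistence than any in step 2; it puts r² at 0.43 with 80% yes at entry and 0.20 with 95%.

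**5. What these figures do not cover.** They describe the entry answer. The gain from the food-insecurity score or from the stratum was not computed, and the documents give nothing to compute it from.

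**The case against.** The strongest reply is that no baseline value of this outcome is documented. A reader might infer that an identical question was asked of everyone at screening and then ignored. The documents do not support that. Someone who qualifies on the food score need not have been asked; the eligibility section gives no question wording, response options or time frame; and SAP 5.3 describes a follow-up item and omits it from the baseline data. This stands, which is why the adjustment should start from baseline food security, which SAP 5.3 says was collected, and use the entry answer only if it is held for all.

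A reader might also infer that the plan breaks its own rule on baseline adjustment. It does not: that clause covers count outcomes only and depends on availability.

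The size is assumed, and the population is selected for hardship, so nearly everyone may have answered yes at entry. This stands too: the gain then falls towards zero. The 15-point effect used for power is likewise not in the documents.

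Finally, a crude risk difference is transparent, prespecified and consistent across both documents, and this is one of seven secondary outcomes. That limits the weight of the point. It does not remove it, because adjusting for a prespecified baseline variable costs very little at this sample size even when the variable turns out to be uninformative.

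**Conclusion.** The point holds as an optional gain in precision. The planned comparison uses no baseline information and no randomisation stratum, although the entry rule creates a possible difference in starting position and a related baseline measure was collected. A reader might take this to mean that the result for hypothesis 4 would be biased or its p-value unreliable; neither follows, since randomisation protects the crude comparison.

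Under the rates in step 2, the variance that adjustment for the entry answer could remove is about 4% to 31% with 60% to 90% yes at entry, about 2% to 10% with 95%, and none with 100%. These figures require that the entry answer was recorded, that it varied and that it persisted, none of which the documents establish.

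The case is better documented for food-security status, which has the same crude test in SAP 8.3 and a baseline that SAP 5.3 says was collected.

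**What to change.** 1. In the protocol's analysis paragraph and SAP 8.3, define the financial-security analysis as a risk difference adjusted for the baseline 0 to 6 food-insecurity score and the randomisation stratum, for example by logistic regression with standardisation. Take the 95% confidence interval and p-value from that model and keep the crude proportions as description.
2. Before naming the stratum, reconcile stratification by condition (protocol Design section, SAP 2.2) with stratification by site (protocol analysis paragraph).
3. State in SAP 5.3 whether the screening answer on making ends meet is held for every participant. If so, add it as a covariate. If not, use entry route: food score 2 or above, or making ends meet only. Entry route can be derived from the food score, because anyone eligible with a score below 2 must have reported trouble making ends meet. It is therefore not a separate measurement, but it lets the model step at 2.
4. Apply the same baseline adjustment to food-security status.

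The cost is SAP wording and a few lines of code, with no new data collection. The downsides are a model-based estimate in place of a raw one, a rule for missing entry answers, and possibly sparse cells if few participants answered no at entry. Standardisation after a regression copes with sparse cells better than full cross-stratification.

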## 6 I. Summary of Changes to the Protocol

7

| Amendments to the Protocol                                             | Approval Date |
|------------------------------------------------------------------------|---------------|
| Added a third primary care site (Regent Park Community Health Centre). | 2024-02-14    |
| Sample size estimation corrected                                       | 2025-07-14    |
| Intervention revised to remove restriction on purchases with voucher   | 2025-07-14    |

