## **Recruitment & Enrollment**

Enrollment will take place within the two primary care sites in Toronto, Ontario (population 2.3 million). Notices of the study will be posted in waiting rooms and examination rooms and study brochures will also be distributed around the primary care sites. The study team will attend team meetings to make clinicians aware of the study. We will facilitate searches of electronic health records to identify potentially eligible patients and will provide clinicians with a list of

potential participants. We will ask clinicians to contact potential participants and, if they are interested in learning more about the study, clinicians will share the patient's phone number or email address with the research assistant or coordinator who will contact the patient to confirm eligibility and consent. If consent is provided, the research assistant will enter participant details in the electronic case report form that will also randomize the participant to one of the two groups. Randomization will be achieved by a web-based interface. After research personnel enter identifying details, the participant will be randomized to one of the two groups. Overall blinding is not possible because participants in the intervention group will be provided with voucher. Outcome assessors will be blinded to the group of allocation.

We expect to recruit at least 1 participant per working day and thus recruiting 390 participants may take up to 19 months. The St Michael's Academic Family Health Team is made up of six physical sites in downtown Toronto and serves approximately 45 000 patients. South Riverdale Community Health Centre is made up of six physical sites and serves approximately 10 000 patients. The collective size of the patient population across sites is approximately 55,000 and the prevalence of diabetes is 7.3 % so we estimate that there are at least 4,000 patients with diabetes and patients with diabetes typically attend appointments every 3 to 6 months and thus there are approximately 12,000 visits for diabetes each year. Based on previous waiting room surveys of patients, we estimate that at least 25 % will meet the inclusion criteria so there should be at least 1,000 patients eligible to participate. If the recruitment rate is slower than expected, we will expand the study to additional sites.

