### **Design, Data Collection & Analysis**

The study is an individual participant, 1:1 allocation, two-arm parallel randomized controlled trial. Allocation will be unblinded to participants and clinicians; outcome assessors and adjudicators will be blinded. Randomization will be stratified by condition: “pre-diabetes” (A1c 6.0 to 6.4) versus diabetes (A1c  $\geq$  6.5).

The trial design including the outcomes will be publicly registered and results reported according to CONSORT and TIDier guidance. We will make individual level participant data available when the study is complete (no identifying information about participants).

An established community guidance panel will contribute to developing the plan to implement the intervention and provide direction in study processes, interpretation and recommendations and may also identify potential additions to the study outcomes.

Study personnel will send the clinicians of participants in each group messages, through the electronic health record, at three, four and five months after randomization reminding them that the patient may be due for a hemoglobin A1c measurement. We will also contact participants by phone and email to remind them about having their hemoglobin A1c checked at 5 months.

The intervention period is six months. We will administer a survey after six months which can be completed by phone, by email, in person during a clinic visit or in person at home and will take approximately 15 minutes to complete. A subset of 20 randomly selected intervention group participants will be prompted to report all foods and beverages consumed the prior day using a validated self-administered 24-hour recall as part of this survey. In a separate subset of 20 purposefully selected intervention group participants, we will conduct interviews to capture the experience of the intervention for qualitative analysis. Prior to contacting participants to complete the survey, we will send a reminder notice by email or mail. Participants in both the intervention and control groups will be compensated \$15 for completing the 6 month follow up survey. The subset of 20 participants will be compensated an additional \$20 when they complete the one-on-one interview which will take approximately 20 minutes.

Hemoglobin A1c will be assessed by a review of the electronic primary care record or based on laboratory testing for study purposes if not ordered for clinical purposes.

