###### 2.2 Trial Design

We conducted an open label, parallel two-arm, 1:1 allocation randomized controlled trial. Randomization is stratified by condition: “pre-diabetes” (A1c 6.0 to 6.4) versus diabetes (A1c  $\geq$  6.5).

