## 7. Sample size

The sample size was estimated based on the power to detect a clinically important 0.04 difference between groups in the primary outcome of the change in hemoglobin A1c. Based on previous trials, we expect a mean change in hemoglobin A1c in the control group of 0, with a standard deviation of 0.013 (1.3%). To detect a 0.004 (0.4%) absolute difference, a sample size of 332 (166 in each group) is required ( $\alpha$  0.05, power 80%). Assuming a 15% rate of drop-out or missing data (e.g. missing hemoglobin A1c measurement), 390 participants (195 in each group) are needed. A total of 390 participants were recruited, with 194 allocated to the intervention group and 196 allocated to the control group.

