### 8.2 Analysis of primary outcome

Hemoglobin A1c will be compared between the intervention and control arm using analysis of covariance (ANCOVA). The covariates will be age, sex, household size, and condition (diabetes versus prediabetes). We will present results of the adjusted and unadjusted models. We will also describe for each group (intervention and control) the baseline, follow-up (6 month) and change (follow-up minus baseline) A1c using mean (with standard deviation) and median (with interquartile range).

In a sub-group analyses, we will assess whether there is a significant interaction between the mean change in hemoglobin A1c and (1) age, (2) sex, (3) condition ("prediabetes" and diabetes), (4) household size, (5) whether prescribed oral diabetes treatment (6) whether prescribed insulin.

We will also use chi-square tests to compare the proportion of participants with "pre-diabetes" (A1c 6.0 to 6.4) at baseline who convert to a normal hemoglobin A1c ( $<6.0$  %) and those who convert to diabetes (A1c  $\geq 6.5$ ), and the number of participants with diabetes at baseline (A1c  $\geq 6.5$ ) who convert to "pre-diabetes" (A1c 6.0 to 6.4) and to normal hemoglobin A1c ( $<6.0$ %).

For the primary analysis, a  $p$ -value of  $<0.05$  will be sufficient to reject the null hypothesis of no difference.

We will address missing outcome data using methods appropriate to their pattern which may include inverse probability weighted analysis. We will address missing baseline characteristic data using methods appropriate to their pattern which may include multiple imputation.

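### The documents do not settle whether randomisation was stratified by site as well as condition; if it was, the primary ANCOVA leaves out a stratifier and is mildly conservative

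*Combined protocol and SAP*

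**What the plan says.** Three places describe the stratification, and each names one factor.

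- Protocol, Design, Data Collection & Analysis: "Randomization will be stratified by condition", meaning prediabetes versus diabetes. Site is not mentioned.
- Protocol, analysis text at the end of Secondary outcome measures: "Randomization will be stratified by site". Condition is not mentioned.
- SAP 2.2: "Randomization is stratified by condition". Site is not mentioned.

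The Summary of Changes lists no change to stratification. Its only entry about sites is "Added a third primary care site (Regent Park Community Health Centre".

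Two covariate lists are given for the primary outcome. SAP 8.2 has "The covariates will be age, sex, household size, and condition (diabetes versus prediabetes". The protocol has an "analysis adjusted for age, sex, whether or not prescribed diabetes oral medicines at baseline, and whether or not prescribed insulin at baseline". Site is in neither list. Baseline A1c adjustment is stated separately, in the protocol's analysis text and in SAP 5.3. Site is also absent from the SAP's subgroup factors (8.2) and its baseline characteristics (6.1).

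**The concern.** A factor used to restrict randomisation should normally be in the primary model. Stratifying removes chance imbalance on that factor, so the treatment estimate varies less from trial to trial. A model without the factor still counts its variance as noise, and so reports a standard error larger than the true one. Intervals come out too wide and the test rejects less often than its nominal level.

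If the site sentence describes what was programmed, no pre-specified model or table reflects that part of the randomisation. A reader cannot tell from the documents whether this is so. While the question stays open, so does the covariate set of the primary analysis.

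Site is also undefined. The protocol says "Enrollment will take place within the two primary care sites in Toronto, Ontario", but its Recruitment & Enrollment section describes each of those two organisations as having six physical sites. A site stratum could mean an organisation or a location.

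**Working it through.** **Plan's own figure.** SAP 7 states: "To detect a 0.004 (0.4%) absolute difference, a sample size of 332 (166 in each group) is required". Inputs there are a difference of 0.4, SD 1.3, alpha 0.05 (taken as two-sided) and power 80%.

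n per arm = 2 × (1.960 + 0.842)² × 1.3² / 0.4² = 165.8, so 166 per arm and 332 in total. This reproduces. Allowing for 15% missing, 332 / 0.85 = 390.6, or 391 against the stated 390. The calculation has no stratification term, so nothing below changes the required sample size.

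**Assumption.** Let R² be the share of outcome variance explained by site. The documents give no value, so 0, 2, 5 and 10% are used. In an ANCOVA, R² refers to the variance left after the other covariates. The SD of 1.3 is kept as the total for simplicity.

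**Standard errors at 166 per arm, near-perfect balance within site.**

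- Reported with site omitted: 1.3 × √(2/166) = 0.1427.
- True: 0.1427 × √(1 − R²). At R² = 10% this is 0.1354, so the reported value is 1/√0.90 = 1.054 times the true one. The 95% half-width is 0.280 where 0.265 would do.

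**Type I error and power.** With 0.4 / 0.1427 = 2.803:

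- True type I error, site omitted: 2Φ(−1.96 / √(1 − R²))
- Power, site omitted: Φ((2.803 − 1.96) / √(1 − R²))
- Power, site included: Φ(2.803 / √(1 − R²) − 1.96)

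| Assumed site R² | Type I error, omitted | Power, omitted | Power, included | Points forgone (from unrounded values) |
|---|---|---|---|---|
| 0% | 0.050 | 80.0% | 80.0% | 0 |
| 2% | 0.048 | 80.3% | 80.8% | 0.5 |
| 5% | 0.044 | 80.7% | 82.0% | 1.4 |
| 10% | 0.039 | 81.3% | 84.0% | 2.7 |

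**Simulation check.** This used 4,000 replicates, N = 332, blocks of four within three sites, and assumed site shares of 60, 25 and 15%. At R² = 10%:

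- The model without site reported a mean standard error of 0.1425, while the estimate's actual SD was 0.137 under no effect and 0.134 under a 0.4 effect. With site the model reported 0.135.
- Type I error was 0.043 without site and 0.054 with it. Power was 80.7% and 83.6%.
- The mean estimate without site was −0.002 when the truth was 0 and 0.396 when it was 0.4, so there is no sign of bias.

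The Monte Carlo error of a simulated type I rate is about √(0.05 × 0.95 / 4000) = 0.003. The simulation therefore supports the direction and rough size of the effect, not its third decimal.

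**Degrees of freedom.** Three organisations need 3 − 1 = 2. Physical locations need at least 12: six plus six, plus at least one for the added centre, gives at least 13 levels.

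**The case against.** The strongest reply is that this is incomplete description and not contradiction. None of the three statements says that its factor was the only one, so stratification by condition and site together would satisfy all of them. That stands, although no place says both were used. The SAP is also consistent with itself: it names condition as the stratifier and puts condition in the ANCOVA. Omitting site is an analysis error only if the protocol's site sentence describes what was programmed.

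The numbers are also conditional. The R² values are chosen, not sourced. The formulas assume near-perfect balance within strata, yet the protocol describes only a web-based interface and gives no block scheme. Missing outcomes would loosen the balance further. Each figure is therefore close to an upper bound for its R², and at R² near zero nothing is lost.

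A reader might infer four stronger things that the documents do not support:

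- **That the result would be biased or the false-positive rate raised.** The effect runs the other way.
- **That power falls below 80%.** It does not under these inputs; the loss is relative to what a model with site would give.
- **That omitting condition from the protocol's adjusted list, or from an unadjusted model, is a comparable or larger loss.** Condition is a cut of baseline A1c at 6.5, and the planned primary analysis adjusts for baseline A1c, which should absorb most of what condition explains. The label unadjusted may itself mean adjusted for baseline only.
- **That every secondary analysis needs the strata.** SAP 8.3 relies largely on t-tests, chi-squared tests and Wilcoxon tests, which take no covariates. Adding strata would mean replacing those methods, and this point does not justify that.

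**Conclusion.** The point holds in a limited form. It is certain that the stratification statements disagree as written and that site is in neither covariate list for the primary outcome. Which factor or factors were used cannot be determined from the documents.

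The statistical consequence depends on site having been a stratifier. In that case the cost is wider intervals and a conservative test, and it is modest: only the 10% case approaches 3 points of power. It is still worth correcting, because the plan is sized at almost exactly 80% power and the remedy needs no new participants.

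**What to change.** 1. Confirm from the web randomisation system which strata were programmed. SAP 7 reports all 390 participants recruited, so this is a settled fact that can be looked up.
2. Make the protocol's design section, the protocol's analysis text and SAP 2.2 state the same factor or factors.
3. Define site as organisation or physical location, and say how the centre added by amendment was handled.
4. In SAP 8.2, include every stratifier used in the primary ANCOVA. If site was one, enter it as a fixed effect alongside condition and baseline A1c. Date the change, and make it before outcomes are compared by arm.

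The cost is a few sentences of protocol and SAP text and about two degrees of freedom out of roughly 330 if site means the three organisations. If it means physical locations the cost is at least 12, with about 332 / 13 ≈ 26 evaluable participants per location on average, or fewer if there are more locations. The secondary analyses can stay as they are.
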